### Data collection and management

Data will be stored in a secure password-protected electronic database hosted by the Brain Injury Centre BOMI following Danish legislation. Over a period of three years, 84 individuals with ABI will be included in the study and assigned a unique trial ID number. Data will be collected prior to the intervention (baseline), at the end of the intervention, and at the six-month follow-up by various questionnaires (Fig. 1 and Table 1). All assessments will take place at the local rehabilitation center and will be done by two to three research assistants blinded to the intervention. Each assistant will receive thorough training in the assessment and will continue to be supervised throughout the study period. Data will be entered directly into a survey and exported into the database to ensure quality of the data. Access to data is restricted to the principle investigator and authorized researchers reported to the Danish Data Protection Agency. Furthermore, the data will be published in peer-reviewed scientific journals and the results will also be presented at national and international conferences.

### Ethical issues

The study has been reported to the Danish Data Protection Agency (registration no. 2016-41-4950) and is registered with the Clinical Trials Gov identifier no. NCT03086031. The Regional Ethical Committee of Copenhagen, Denmark, has stated that the study does not need their approval (komitélovens §§1 and 2). The study will be carried out according to the local legal and regulatory requirements and data will be handled according to the guidelines given by the Danish Personal Data Protection Agency.

All participants must give written and oral informed consent to participate in the study, including their consent to publish the results. If any participants are under the age of 18 years, they will provide a verbal acceptance while their parents will complete the written consent.

We expect a very low risk of adverse effects. However, increased fatigue in the intervention group could occur since a more intense program is followed and the test situation might be exhausting to some patients. Furthermore, VR could for some participants be perceived as stressful and inclusion of the family caregivers could result in a higher risk for intra-family conflicts. However, the sessions in the family intervention program includes psychoeducation in how to recognize, handle, and cope with situations that might escalate emotionally. All adverse effects will be reported and participants have the possibility to contact the rehabilitation team by telephone or email throughout the study.

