### Blinding

Because of the nature of the study, it will be clear to most participants whether they are allocated to the VR intervention or the control group. Thus, it is not possible to blind either the participants or the rehabilitation team, but they will be asked not to disclose any details about the allocation or the content of the VR. The two independent research assistants will be trained to administer the assessments and will be blinded to the allocation when entering data into the database. The researchers and the statistician performing the data analysis are blind to the treatment arm in which the participants are allocated. The rehabilitation team and the research assistant will only be involved in the data collection and will therefore not participate in the data analyses.

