### A description of the manual-based VR interventions

This manual-based VR study comprises the following three phases:Initial assessment: Within two weeks after the referral to the study, each patient will meet with the case manager in the municipality (brain injury coordinator). Here, a more thorough interview will ensure that the inclusion criteria are met and, in addition, asses the patient’s readiness for VR. Moreover, the participant will be fully informed about the content of the study, how participation is voluntary, and how they are free to withdraw at any time during the study. If written informed consent is obtained, each patient is assigned a unique trial ID number and baseline questionnaires will be filled out together with the following socio-demographic, employment, and clinical data: gender; date of birth; residence; civil status; nationality; income; pre-injury employment and education status; pre-injury occupation status; length of education; time since the brain injury; type and location of the brain injury; number of days hospitalized; the date of discharge; clinical diagnoses or any relevant medical events; and alcohol consumption or abuse. Participants will then be randomly assigned to either the VR intervention or the conventional VR. At last, each patient included in the VR intervention group will be asked to choose at least two family members to participate in the family intervention and one family caregiver which will participate actively in the individual sessions and serve as future support and resource facilitator to assist them in returning to work. This initial assessment will take approximately 50 min and the patient will have the opportunity to ask questions throughout the entire assessment. To exclude recruitment bias, patients that meet the eligibility criteria but refuse to participate in the study will be asked a few questions about their refusal. Hereafter, the patient will be contacted by external testers and baseline testing will be completed.The VR intervention program: The VR intervention lasts for a total of 6–9 months and consists of, first, six different modules (approximately three months) that are individually planned based on the patient needs and goals and, second, a work placement program (approximately 3–6 months). To ensure a uniform procedure of each of the different modules, comprehensive “standard operating procedures” (SOPs) will be developed by the rehabilitation team at the Brain Injury Centre before the beginning of the VR intervention. All members of the rehabilitation team (which includes six neuropsychologists, eight occupational therapists, and four physiotherapists) are already experienced in the VR intervention program and exceedingly specialized in ABI rehabilitation. They will go through a one-day workshop to be thoroughly introduced to the specific study protocol and the SOPs as recommended by Holmes et al. [31]. The six modules will be grouped into: (1) individual therapies, which includes neuropsychological sessions (10 h), balance between work and everyday life (20 h), and job matching (10 h); (2) grouped-based therapies, which includes psycho education (18 h), mindfulness (15 h), and physiotherapy training (15 h); (c) a manualized family intervention program (eight sessions of 90 min) [32] and an individual caregiver coaching, supporting the caregiver in assisting the patient using the different strategies and tools learned in the intervention in everyday life and at the workplace (12 h); (4) an individual work placement program including work practice (3–6 months), supported employment where the rehabilitation team is at the work place (30 h), and the development of a post-rehabilitation plan (4 h). The modules are planned based on the participant’s needs and goals thus, the length, duration, structure, and composition of the program will vary from patient to patient. The individual sessions and group sessions are delivered either in parallel or in serial depending on the patient.Group sessions will take place at the Brain Injury Centre BOMI and the individual sessions will most often take place in the patient’s home. The individual work placement intervention will take place at relevant workplaces, the patient’s current workplace, or at a new workplace found by the municipality or the Brain Injury Centre BOMI, depending on the individual case.Post-trial evaluation: An evaluation of the VR intervention will be performed by a self-developed semi-structured interview of each patient. Here, questions related to the recruitment procedure, the modules of the study, the timing of modules, and the coaching by the rehabilitation team will be collected. Furthermore, all case managers at the municipalities that referred participants to the study will be asked about their experiences and level of satisfaction.

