
### The conventional VR provided by the municipalities (usual care)

Individuals allocated to the control group will receive the conventional VR program provided by the municipalities over the same period of time. Thus, the participants in the control group will receive VR support by the local municipal authority that may vary in content and intensity. As for the intervention group, each individual in the control group will select a family caregiver that will go through the same questionnaires as the caregivers in the VR intervention group regarding HRQoL and functional level.

Furthermore, the case manager at the municipalities is obliged to: (1) refer patients to the study; (2) hand out the baseline questionnaires to the participants and their family caregivers; and (3) complete a questionnaire about each participant at the beginning and end of the study, and again at the six-month follow-up.

An evaluation of the conventional VR provided by the municipalities will be performed by the rehabilitation team using a self-developed semi-structured interview of each patient.

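### The only adverse-effect contact named is the team that delivers the VR arm, so counts of spontaneous reports are open to unequal ascertainment between arms

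*Protocol article*

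**What the plan says.** The Ethical issues section of the protocol article opens its account of harms with "We expect a very low risk of adverse effects". It then names four possible harms: greater fatigue, exhaustion from the test situation, stress from VR, and conflict within the family. Two are worded as an increase: "increased fatigue in the intervention group could occur since a more intense program is followed" and "inclusion of the family caregivers could result in a higher risk for intra-family conflicts". On reporting it says "All adverse effects will be reported and participants have the possibility to contact the rehabilitation team by telephone or email throughout the study".

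The rehabilitation team is the Brain Injury Centre staff who deliver the programme. Its members "are already experienced in the VR intervention program and exceedingly specialized in ABI rehabilitation" (A description of the manual-based VR interventions). In the other arm, "participants in the control group will receive VR support by the local municipal authority that may vary in content and intensity" (The conventional VR provided by the municipalities). That section gives the municipal case manager three duties: referral, handing out baseline questionnaires, and completing a questionnaire on each participant at the start, the end and six months. Adverse effects are not mentioned among them. The same section has the rehabilitation team interview each patient to evaluate conventional VR.

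Under Blinding, participants and the rehabilitation team cannot be blinded, but "they will be asked not to disclose any details about the allocation or the content of the VR". No exception for harms is stated.

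**The concern.** Spontaneous reporting depends on opportunity. A VR patient sees the named contact for months. A control patient would have to telephone or email staff who do not treat them. Even if both arms had the same true risk, the counts could differ.

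The direction is not certain. More contact favours more reports in the VR arm. An unblinded provider hearing complaints about its own programme could instead lead to fewer being recorded. The non-disclosure request may add friction when harms are mentioned to the blinded assessors, because fatigue from the programme, stress from VR and family conflict are hard to describe without touching on its content.

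What is at stake is how any adverse-effect count in the trial report is read. Readers will set the two arms' numbers side by side whether or not a test is planned, and two of the harms the article anticipates are themselves comparative.

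**Working it through.** The article states no adverse-effect rate, threshold or safety power, so there is no figure to reproduce. The check covers contact by arm, what each mitigating provision supplies, and the size that unequal capture could have.

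**1. Nominal team contact in the VR arm** (hours from A description of the manual-based VR interventions)
- Individual therapies: 10 + 20 + 10 = 40 h
- Group therapies: 18 + 15 + 15 = 48 h
- Family programme: 8 sessions × 1.5 h = 12 h
- Caregiver coaching: 12 h
- Supported employment at the workplace: 30 h
- Post-rehabilitation plan: 4 h
- Total: 40 + 48 + 12 + 12 + 30 + 4 = 146 h

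This is nominal, because the same section says the programme varies from patient to patient. For controls, the only contact with this team that the article describes is the evaluation interview.

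**2. What could offset the asymmetry**
- *Evaluation interview.* Its stated purpose in controls is to evaluate conventional VR. The topics listed for the VR-arm interview are recruitment, modules, timing and coaching. Both arms are interviewed, so it does not equalise contact.
- *Case manager questionnaire.* It is completed for each participant at three times. Its content is not shown, so it cannot be assumed either to capture harms or to miss them.
- *Table 1 scales.* DMFS (fatigue), HADS (anxiety and depression, in patients and caregivers), FACES-IV (family interaction) and the Caregiver Burden Scale are measured at baseline, end and six months. Data collection and management assigns all assessments to research assistants described as blinded. These scales do not depend on spontaneous reporting. However, they are scores at two post-baseline times, not the adverse effects that Ethical issues promises to report. Short episodes between visits can be missed, and no item addresses exhaustion from testing.

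**3. Size under assumptions**

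Expected reports = n × true risk × probability of capture, with n = 42 per arm (Sample size and power). If true risk is equal, the apparent risk ratio is capture in VR ÷ capture in control, whatever the true risk. The 20% risk and all capture probabilities are assumptions.

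| Capture VR | Capture control | VR reports | Control reports | Apparent ratio |
|---|---|---|---|---|
| 0.9 | 0.9 | 42 × 0.2 × 0.9 = 7.6 | 7.6 | 1.0 |
| 0.9 | 0.7 | 7.6 | 42 × 0.2 × 0.7 = 5.9 | 1.29 |
| 0.9 | 0.5 | 7.6 | 42 × 0.2 × 0.5 = 4.2 | 1.8 |
| 0.9 | 0.3 | 7.6 | 42 × 0.2 × 0.3 = 2.5 | 3.0 |

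A second assumed set, 0.8 in VR against 0.5 to 0.2 in controls, gives 6.7 against 4.2 to 1.7 reports, a ratio of 1.6 to 4. If capture were lower in the VR arm, the ratio would fall below 1.

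**4. What the VR arm can show alone**

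With no events in 42 patients, the exact upper limit is 1 − 0.025^(1/42) = 8.4% (two-sided 95%) or 1 − 0.05^(1/42) = 6.9% (one-sided 95%). This needs no control data, but it does assume that events in the VR arm are fully captured.

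**The case against.** The strongest reply has four parts.

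- **The route is not exclusive.** The reporting sentence joins two statements: that effects will be reported, and that participants may contact the team. It does not say that reports go only through that team, and it offers the contact to participants of both arms. A reader might infer an exclusive route, but the text does not support that. What stands is that it is the only contact named.
- **No comparison is planned.** No between-arm analysis of adverse effects appears in the hypotheses, Table 1 or Statistical analysis. The low expected risk carries no rate or threshold. A reader might conclude that the trial cannot test this expectation. No such test was proposed, and the VR-arm risk can be bounded from that arm alone.
- **The main harms are measured in both arms.** A reader might conclude that harms cannot be compared at all. That fails: DMFS measures fatigue directly, and the other three scales are the nearest measures of distress and family strain. This objection stands and sharply limits the concern. It does not reach event counts.
- **An article condenses.** Adverse-event definitions and forms may sit in the full protocol, so their absence is no fault. That also stands. The point rests on the contact the article does name and on who that contact treats.

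Two further arguments are weak. Nothing in the article has the treating team decide causality. The non-disclosure request sits among the blinding provisions, and nothing suggests it stops a participant from telling the unblinded team about a problem. It matters mainly for reports to the blinded assessors.

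**Conclusion.** The concern holds in a limited form. The one contact named for adverse effects is the unblinded provider of one arm, and no counterpart is named for controls. Counts of spontaneous reports are therefore open to unequal ascertainment, and a raw comparison could mislead in either direction.

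The size is unknown. The ratios of 1.29 to 3.0, or 1.6 to 4, rest entirely on assumed capture probabilities; equal capture gives 1.0. The conclusion also assumes that no arm-neutral elicitation of harms exists in documents not shown here.

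This is a modest point about interpretation and a cheap improvement. It does not affect the primary outcome, and it does not prevent a comparison of fatigue, distress and family strain through the Table 1 scales.

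**What to change.** 1. At the end-of-intervention and six-month assessments, have the blinded research assistants ask both arms the same short closed checklist on the four harms named in Ethical issues. Word the items without reference to programme content and record events regardless of cause.
2. State under Blinding that the non-disclosure request does not apply to reporting harms.
3. Keep the telephone and email contact for participants' care. Present reports received that way separately, by source, without a between-arm comparison.
4. Read the checklist results alongside DMFS, HADS, FACES-IV and the Caregiver Burden Scale.

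The cost is one short form at two visits that already take place, and a sentence each under Blinding and Ethical issues. The downsides are a few more minutes per assessment, a small risk that an answer reveals the allocation, and a higher recorded event count than spontaneous reporting would give. The checklist equalises the opportunity to report. It does not remove the influence of participants knowing their arm, and the report should say so.

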### Sample size and power

The primary endpoint “hours at work/study per week” is assumed to follow a Poisson distribution with an overdispersion of 4. Under this assumption, the relation between average hours at work for the conventional VR treatment, the expected surplus of hours by the VR intervention and the study power is calculated for a study with n = 42 + 42 = 84 participants. Figure 3 shows this relation where, for instance, a study with 10 h of work for the conventional VR treatment and 14 h of work for the VR intervention leads to a study power of 0.8 at level alpha = 0.05.

**Fig. 3 Fig3:**
[figure not shown]
The *x-axis* depicts the average hours at work/study per week for the conventional VR treatment and the *y-axis* the average surplus obtained from the VR intervention. The *colors* indicate the study power at level alpha 0.05 under these expectations for a study with 42 + 42 = 84 participants. The *black line* indicates the combinations obtaining a power of 0.8

### Statistical analysis

Data analysis will be conducted using the statistical program R version 3.2.2. Baseline characteristics of the participants will be reported to ensure homogeneity between the VR intervention and the control group (reported as mean and standard deviation for continuous variables and proportions for categorical variables). Differences between baseline characteristics for continuous variables will be tested by an independent samples *t*-test or a Mann–Whitney U test dependent on the distribution of the data. Categorical variables will be analyzed by a Chi-square test. If any significant differences between the VR intervention and the control group are found, these will be adjusted for in the downstream analyses.

The differences between the VR intervention and the control group for the primary and secondary outcomes will be analyzed using repeated measurements statistical tools and multilevel analysis, including possible confounders (e.g. age, gender, ABI severity, socioeconomic status pre-injury, education, or recruitment site). *P* values and 95% confidence intervals will be provided and *P* < 0.05 will be considered statistical significant.

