### Randomization

To avoid confounding between the VR intervention and the control group due to random probability, the number of cases and controls within each of the enrolled municipalities is set to be the same (+1/–1). Due to the prospective nature of the inclusion, which practically means that the number of patients included within each municipality is not known a priori, the randomization is performed by randomly assigning the first patient within each municipality to either the VR intervention or the conventional VR program. The following patient (within each municipality) is then assigned consecutive to the other group and so forth. This randomization scheme ensures equal distribution of cases and controls, both within each municipality as well as in time, avoiding confusion of these two factors. Controlling the distribution over time is central in such a study where some variation over the trial period due to protocol familiarity of the rehabilitation team at the Brain Injury Centre may be expected.

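### Baseline significance tests decide which covariates enter the outcome models; this forgoes power without inflating overall type I error, and a fixed prognostic set should replace it

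*Protocol article*

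**What the plan says.** All the covariate text is in the Statistical analysis section of the protocol article, and it gives two routes into the model.

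- **Route 1, by test.** For continuous variables, "Differences between baseline characteristics for continuous variables will be tested by an independent samples" t-test or a Mann–Whitney U test. For the others, "Categorical variables will be analyzed by a Chi-square test". The consequence is then stated: "If any significant differences between the VR intervention and the control group are found, these will be adjusted for in the downstream analyses".
- **Route 2, by example.** The outcome models are described as "including possible confounders (e.g. age, gender, ABI severity, socioeconomic status pre-injury, education, or recruitment site". This does not depend on the baseline tests, but it is a list of examples joined by 'or'.

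The model itself is given only in general terms: outcomes "will be analyzed using repeated measurements statistical tools and multilevel analysis", with *P* "< 0.05 will be considered statistical significant". Table 1 shows hours at work or study measured at baseline, end of intervention and six-month follow-up. The Randomization section balances the arms by municipality: "the number of cases and controls within each of the enrolled municipalities is set to be the same", to within one patient.

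**The concern.** Route 1 is a rule that the article states, not a detail left for later. It selects on the wrong property. A covariate earns its place in a randomised comparison by predicting the outcome, and the p-value of a baseline difference carries no information on that. A variable unrelated to hours worked can enter because it happened to differ, while a strong predictor with a moderate difference stays out.

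The final model for the primary endpoint would therefore depend on the observed baseline data. The precision available from variables already collected would not be secured, above all from baseline hours and from municipality, the unit within which allocation is balanced.

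**Working it through.** **Inputs.** From the article: 42 per arm; means of 10 and 14 h/week, with hours "assumed to follow a Poisson distribution with an overdispersion of 4"; alpha 0.05, taken as two-sided. The initial-assessment description lists 15 baseline items, and the 13 outcome measures taken at baseline in Table 1 bring the count to about 28. Assumed, because the documents do not give them: independent baseline tests, and the correlation (rho) or R² between covariates and outcome.

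**1. The plan's own power figure.** With variance = 4 × mean, the arm variances are 40 and 56. SE = √((40 + 56)/42) = 1.512. Power = Φ(4/1.512 − 1.96) = Φ(0.686) = 0.754, against the stated 0.80. That gap is a separate matter. It is used here only to set the scale: average variance 48, so the standardised effect is 4/√48 = 0.577, and unadjusted power in simulation is 0.74–0.75.

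**2. Chance flags.** 1 − 0.95^15 = 0.54. With 28 variables, 1 − 0.95^28 = 0.76.

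**3. Missed imbalance.** An observed difference must reach about 1.96 × √(2/42) = 0.43 SD to be flagged. If a systematic imbalance of 0.3 SD exists, the chance of flagging it is Φ(0.3 × √21 − 1.96) = Φ(−0.585) = 0.28. At 0.5 SD it is 0.63.

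**4. What Route 1 alone selects.** Take 3 prognostic variables among 15. None of the three is selected with probability 0.95³ = 0.86 (simulated 0.85–0.86). At least one of the 12 noise variables is selected with probability 1 − 0.95^12 = 0.46 (simulated 0.45–0.47).

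**5. Power for one covariate, Route 1 against always adjusting** (simulated, 42 + 42):

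| Assumed rho | Effect (SD) | Rule | Always adjusted | Difference |
|---|---|---|---|---|
| 0.3 | 0.577 | 0.745 | 0.775 | 0.030 |
| 0.4 | 0.55 | 0.705 | 0.768 | 0.063 |
| 0.5 | 0.577 | 0.755 | 0.850 | 0.095 |
| 0.6 | 0.55 | 0.717 | 0.873 | 0.156 |
| 0.7 | 0.577 | 0.764 | 0.954 | 0.190 |

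The two effect sizes come from separate runs; compare within rows.

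**6. Both routes together.** Suppose all six listed confounders are always included, the prognostic ones are among them, and significant extras are added. Power is then 0.814 against 0.823 for the six alone (total R² 0.25), and 0.919 against 0.927 (R² 0.45). The loss is about 1 point. Type I error is 0.057 against 0.057, and 0.051 against 0.052 (3,000 runs, so the same within simulation error).

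**7. Type I error of Route 1.** Overall it is 0.047, 0.044 and 0.035 at rho 0.3, 0.5 and 0.7, and 0.041–0.045 with 3 prognostic variables among 15. Among trials whose baseline p lies between 0.05 and 0.30 (about a quarter of trials), it is about 0.06 at rho 0.4 and 0.09 at rho 0.6, against 0.05 when the covariate is always in the model.

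**The case against.** The strongest reply is that Route 1 is not the only way in. The listed confounders can enter without any test, and step 6 shows that the rule then costs about 1 point of power. Baseline hours may also already be used, because hours are measured at all three times and the analysis is a repeated-measurements one; recruitment site fits naturally in a multilevel model. The exact covariate list and parametrisation are commonly left to a SAP, which is not shown. All of this stands as a limit on the size of the problem. It does not rescue the rule: the list is open and guarantees no variable, and a SAP that dropped the trigger would contradict the published text.

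A reader might infer four stronger things that the document does not support.

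- **That the rule inflates type I error.** Overall it is at or below nominal. The 0.06–0.09 is conditional on a moderate unadjusted imbalance and is not the trial's error rate. Choosing freely among subsets of the six confounders after seeing results would give 0.13–0.16 in the worst case, but nothing in the article says that this will be done.
- **That power falls below an unadjusted analysis to any material degree.** Under the rule it is about the same (0.73–0.75 against 0.74–0.75 with 15 variables). What is lost is a gain, and its size rests on assumed correlations. Entry is limited to at most 15 h/week, which narrows the range of baseline hours, so the lower correlations are plausible for that variable.
- **That the baseline tests can only detect chance.** Here only the first patient in each municipality is randomised and the rest alternate, so assignment is predictable and a difference could reflect selection. The tests remain a weak detector of that (step 3).
- **That baseline hours and municipality are left out.** They are not secured, which is a weaker statement.

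**Conclusion.** The concern holds in limited form. Selecting covariates by baseline significance is a stated rule and a poor one: it responds to imbalance rather than prognosis, has about a 54% chance of at least one flag under independence, and usually misses an imbalance of 0.3 SD. The open confounder list does not repair it.

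The cost is power not gained: about 3 to 16 points for a covariate with correlation 0.3 to 0.6 that depends on the rule alone, down to about 1 point if all six listed confounders are always fitted. These figures rest on assumed correlations and on normal-theory simulation at 42 per arm. Overall type I error is not raised. The change is worth making because it is nearly free, not because the trial's conclusions would otherwise be invalid.

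**What to change.** Delete the baseline significance tests and the sentence that makes adjustment depend on them. Report baseline characteristics descriptively by arm.

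Replace the list of examples with a named set, used whatever imbalance is observed:

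- the outcome's own baseline value (for the primary endpoint, baseline hours), as a covariate or through a stated repeated-measures parametrisation;
- municipality;
- a short prognostic list, for example age, ABI severity (with its measure named) and time since injury.

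Whether municipality is a fixed or random effect can be left to the SAP.

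The cost is a rewording of about two sentences and a few degrees of freedom. A single covariate with no prognostic value lowers simulated power only from 0.741 to 0.736. The set can be built from data the article already plans to collect.

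### Baseline significance tests decide part of the covariate set, next to an open list of possible confounders, so the primary model is not fixed before the data are seen

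*Protocol article*

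**What the plan says.** The Statistical analysis section of the Protocol article gives two routes by which a covariate can enter the outcome models.

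- **Test-triggered route.** The stated purpose is homogeneity: "Baseline characteristics of the participants will be reported to ensure homogeneity between the VR intervention and the control group". For the tests, "Differences between baseline characteristics for continuous variables will be tested by an independent samples" t-test or by Mann–Whitney, and "Categorical variables will be analyzed by a Chi-square test". The consequence is "If any significant differences between the VR intervention and the control group are found, these will be adjusted for in the downstream analyses".
- **Untested route.** The next paragraph describes repeated-measures and multilevel models for the primary and secondary outcomes, "including possible confounders (e.g. age, gender, ABI severity, socioeconomic status pre-injury, education, or recruitment site". No baseline test is required here, but *possible*, *e.g.* and *or* commit to no particular variable.

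The section ends with the rule that P "< 0.05 will be considered statistical significant". Applying that threshold to the baseline tests is a reasonable inference rather than an explicit statement. The items available for testing are listed under the initial assessment in the description of the VR interventions. They run from gender to "number of days hospitalized; the date of discharge; clinical diagnoses or any relevant medical events; and alcohol consumption or abuse". Which of them will be tested is not said.

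**The concern.** A covariate is worth adjusting for when it predicts the outcome. The P value of a between-arm comparison measures something else, namely how large the imbalance is relative to sampling error at this sample size. A rule based on it can bring in variables that are unrelated to hours worked, and can pass over a strong predictor whose imbalance falls just short of significance. Nor can such tests secure homogeneity, because a non-significant result with 42 per arm still allows a sizeable difference.

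The covariates of the primary model would then be known only after the baseline data have been tested. What is at stake is precision, and a primary estimate that changes with whichever variables the tests select. A later analysis plan that completed the open list would not remove this, because the trigger would still operate on top of it.

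**Working it through.** **Inputs.** From Sample size and power: the power "is calculated for a study with n = 42 + 42 = 84 participants", with 10 h against 14 h per week, a Poisson outcome with overdispersion 4, alpha 0.05 and stated power 0.8. From the initial assessment: 15 items, or 16 if type and location of injury are counted separately. Assumptions: two-sided tests, variance = 4 × mean, independent baseline tests at 5%, and the correlations given below.

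**1. The plan's own power.** The variances are 4 × 10 = 40 and 4 × 14 = 56, so SD = √((40 + 56)/2) = √48 = 6.9 h and the planned effect is 4/6.9 = 0.58 SD. Two-sided power with 42 per arm is 0.754, not quite the stated 0.8. That value is read from a figure that is not shown, and this point does not depend on it. About 0.75 is the unadjusted reference below.

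**2. Imbalance needed to trigger adjustment.** t(0.975, 82) × √(2/42) = 1.989 × 0.218 = 0.43 SD. A true difference of 0.3 SD would be found significant only 28% of the time.

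**3. What an untriggered imbalance can do.** Shift in an unadjusted estimate = correlation × imbalance × SD. Just below the threshold:

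| Assumed correlation with hours | Shift |
|---|---|
| 0.3 | 0.3 × 0.434 × 6.93 = 0.9 h |
| 0.5 | 0.5 × 0.434 × 6.93 = 1.5 h |
| 0.7 | 0.7 × 0.434 × 6.93 = 2.1 h |

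The planned difference is 4 h. These shifts apply only if the variable does not enter through the untested route.

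**4. How often the trigger fires by chance.** 1 − 0.95^15 = 0.54 and 1 − 0.95^16 = 0.56. The expected number of triggers with 15 tests is 15 × 0.05 = 0.75.

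**5. Effect on the analysis.** Simulation used 42 per arm, a normal outcome, 16 baseline variables of which three are prognostic (assumed joint R² of 30%), and an effect of 0.58 SD.

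| Covariates in the model | Power |
|---|---|
| None | about 0.74 |
| Trigger rule alone | about 0.73 |
| Three prognostic, fixed | about 0.86 |
| Three prognostic, fixed, plus trigger | about 0.85 |

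- *Few or none of the listed confounders entered:* the trigger rule alone gains nothing over no adjustment. Its type I error is about 0.04, slightly conservative. The chance that none of the three predictors is triggered is 0.95³ = 0.86. With a single prognostic variable among 15, the rule gave power of 0.74 to 0.75, against 0.85 (correlation 0.5) or 0.96 (correlation 0.7) when that variable was fixed in advance.
- *Prognostic confounders always entered:* power was 0.846 to 0.849 with the trigger and 0.860 to 0.865 without it. At a joint R² of 40% the values were 0.897 and 0.910. Type I error was 0.046 to 0.050. The trigger still added at least one of the 13 noise variables in about half of trials (1 − 0.95^13 = 0.49). In those trials it moved the estimate by 0.3 h on average, and by more than 0.65 h in a tenth of them. It changed the significance verdict in about 3% of trials with a true effect.

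**The case against.** The strongest reply is that the test-triggered sentence is not the whole plan. A reader might infer from it that covariates enter only after a significant baseline test, so that the plan mostly adjusts for noise and leaves real imbalances alone. The document does not support that. The following paragraph brings in age, ABI severity, education, recruitment site and others with no test. If those enter, the large power contrast disappears and the trigger costs only 1 to 2 points. This stands, and it limits the size of the point.

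A reader might also infer an inflated error rate. That is not supported either: overall type I error is near 0.05 or a little below. An error of 6 to 9% does appear among trials with a non-significant imbalance of 0.25 to 0.42 SD in a predictor (correlation 0.3 to 0.6), but this is a property of any unadjusted analysis and is not created by the rule.

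Three further caveats stand:

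- The simulations use a single follow-up outcome, not the planned repeated-measures model with baseline hours.
- The 54 to 56% assumes independent tests, although items such as income, education and occupation are related. It also assumes chance imbalance, whereas the Randomization section alternates allocation after the first patient in each municipality, so differences may not be purely random.
- Completing an open list is commonly left to the analysis plan, so the open list by itself is no defect.

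None of this defends the trigger, which is a stated rule and brings no gain in any setting examined.

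**Conclusion.** The point holds in a limited form. A stated, data-driven trigger sits beside a list that fixes nothing, so the primary model is undefined until the baseline tests have been run.

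The harm ranges from small to moderate according to what the open list supplies. At the low end it is 1 to 2 points of power and an arbitrary addition in about half of trials. At the high end, power stays at 0.73 to 0.75 where about 0.86 was available. The high end rests on an assumed joint R² of 30% and on few or none of the prognostic variables being entered. The document gives no correlations. The 0.43 SD threshold needs only the stated sample size and a two-sided 5% test.

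The change is worth making because it is nearly free, not because the primary result would otherwise be invalid.

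**What to change.** Delete the baseline significance tests and the sentence that makes adjustment depend on them, and report the baseline table descriptively.

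Before any data are seen, name one small set of prognostic covariates recorded before assignment:

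- baseline hours at work or study for the primary outcome, or the baseline value of each secondary outcome;
- municipality;
- a few of age, ABI severity (with its measure named), education and time since injury.

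Use this set in the primary model and all secondary models, whatever balance is observed. Models with extra imbalanced variables may be shown only as labelled sensitivity analyses. Read in order, the initial-assessment text places the external baseline testing after assignment, so the timing of those baseline values should be checked before they are used as covariates.

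The cost is a few sentences in the analysis section, with no extra patients. In degrees of freedom it is 1 for the baseline value, 3 for municipality with four sites, and 2 to 4 for the remaining covariates entered as single terms, so 6 to 8 in all.
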